##### Baseline Assessment:

- Using established coded data transfer methods between Public Safety Medical and the Harvard TH Chan School of Public Health. Public Safety Medical will transfer the results of the last existing fire department medical examination to the Harvard Chan research team for consented participants only.
- Medical exam data that will be provided to the study team for consented IFD/ Fishers subjects include: at rest and maximal heart rate, systolic and diastolic blood pressure, heart rate recovery, electrocardiographic findings at rest, hip and waist circumference, body composition, data regarding the grip strength, leg-press and push-ups performed, and routine lab values (e.g. lipid panels, hs-CRP and glucose).
- The medical exams will be supplemented by a comprehensive nutritional-lifestyle questionnaire (see attached). The survey instrument combines our existing mMDS with other validated scores and nutrition questionnaires. It also includes items on physical activity and other health behaviors to adjust for appropriate covariates. These questionnaires will be self-administered online via Qualtrics on a password-protected site. The comprehensive nutritional-lifestyle questionnaire should take between 20-45 minutes to complete.

In addition, the baseline assessment will include anthropometric measures (height, weight and body fat estimates (Tanita) and resting blood pressure will be taken in private areas of the fire houses by trained Public Safety Medical clinical staff, during work hours. Height will be measured in the standing position with a standard clinic stadiometer. Waist circumference will be assessed by using a tape measure snugly around each participant’s waist at the level of the iliac crests and measuring the circumference after expiration. Body weight will be measured with bare feet and in light clothes on a calibrated scale. Body fat will be estimated using a Bioelectrical Impedance Analyzer (Tanita). Blood pressures will be measured using an appropriately sized cuff with the subject in the seated position in a resting state.

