### **Follow-up Assessments:**

Every consented participant (regardless of intervention assignment) will be requested to complete the following every 6 months over 4 additional visits after the baseline assessment over the two years of the study:

The comprehensive nutritional-lifestyle questionnaire will be repeated (detailed above), as will the anthropometric measures (height, weight and body fat and resting blood pressure) will be collected in the same manner as described above for the baseline assessment.

Every 12 months, the Fire department provided, annual occupational medicine examinations (part of the firefighters’ usual care unrelated to the present study) will be provided by Public Safety Medical as per existing IFD/ Fishers policies. For consented participants ONLY, the medical exam results will be transferred to the Harvard Chan research team using the same established coded data transfer methods as described above for the baseline assessment of the same data points.

Consented participants will be assigned to Group 1 (Phase 1 nutritional intervention) or Group 2 (No intervention) according to their fire station’s cluster randomization.

For the nested biomarkers study the recruitment of participants will start in phase II following the below timeline:

Figure1. Current parent study timeline and biomarkers proposal timeline (in orange, the proposed study timeline)

[figure not shown]

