The initial and periodic group educational sessions with larger groups (up to 100 firefighters) will be led by the Harvard investigators and the local medical team (Public Safety Medical) and held in fire department classrooms. These will be followed-up by more frequent, smaller group (5-20 firefighters) diet and fitness sessions in fire house classrooms and kitchens by our Indiana-based dietitian and Health/Fitness Specialist, [name]. [name] is contracted with PSM and has a long experience working with firefighters. The sessions may include: didactic presentations, interactive discussions and cooking demonstrations that follow the general recommendations (see below).

Specific topics that we plan to address in the group educational sessions include:

1. Basic Mediterranean Diet principles;
2. The benefits of Olive oil and nuts and how to introduce them into the diet;
3. Overcoming Challenges while following a Mediterranean Diet;
4. How to plan a weekly menu and shopping list;
5. How to choose wisely when eating out (restaurants/parties);
6. Making smart choices regarding "Fast food".

We may also provide in-person chef-led, Mediterranean cooking demonstrations at fire stations in the intervention group. Some of the general educational sessions and cooking demonstrations may be videotaped or otherwise adapted for internet accessibility on the study website.

All of the educational sessions and materials will be centered on the principles and general recommendations outlined in the table below.

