†Optional and only for habitual drinkers without alcohol-related health problems.

‡Sofrito is a sauce made with tomato and onion and/or garlic, slowly simmered with olive oil.

§Homemade sweets are preferable to store-bought or commercially-produced sweets.

||Discouraged.

JOEM • Volume 58, Number 3, March 2016

Participants may also have access to additional discounted food options during the course of the study as follows:

1. Discount coupons obtained directly from producers which can be redeemed at Kroger and other local stores. For example, Barilla pasta has pledged its support to provide coupons for “Barilla Plus”, a line of pastas which combine ALA-3- enriched whole grain and legume flours to produce a high fiber, higher protein product yielding delicious pasta that is more nutritious and promotes better glucose metabolism than typical pasta from refined flours.

2. “Starter” supplies of extra-virgin olive oil, avocados and nuts and for fire house kitchens at no cost, along with coupons and options for obtaining additional product at discounted prices directly through food companies partnering with the study.

3. Encourage and facilitate access to farmer’s markets and produce from local community gardens within the City of Indianapolis and surrounding area.

According to each participant’s preference, they may sign up for either email or text message encouragement and reminders during the intervention. For those opting in to this option, they will receive brief text or email messages 2-4 times per week reinforcing the healthy dietary and lifestyle principles as discussed above.

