and longitudinal data analysis, as needed. Differences in the mean values of a quantitative variable between two groups will be assessed using the independent t-test whereas differences in mean values among three or more groups will be examined using the analysis of variance (ANOVA) technique (or non-parametric Wilcoxon and Kruskal-Wallis tests, respectively, as appropriate). Differences in qualitative characteristics will be compared using the chi-square test, or Fisher's exact test, or McNemar's test (for paired comparisons), as appropriate. Statistical significance for all analyses will be  $p < 0.05$ , and all tests will be two-tailed.

Phase 1: During the first 12 months of the nutritional intervention, **groups 1 (Mediterranean Diet intervention) and 2 (no intervention) will be compared directly on an intention to treat basis according to the randomization of each participant's fire house.** As several outcomes will be assessed on each participant throughout the study (3 annual medical exams and 5 semi-annual assessments (where weight, mMDS, etc. will be evaluated)), repeated measures techniques, such as mixed modeling and generalized estimating equation models, will be utilized to estimate changes over time on key outcomes. We will take into consideration the specific variance-covariance structure of correlated measurements. After adjusting for baseline and time-dependent covariates, changes in the outcomes of interest will be assessed and compared among groups. We expect our greatest power to be for within-group changes (paired comparisons).

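### Section 5.1 adjusts the intention-to-treat comparison for time-dependent covariates without excluding those that the intervention could change

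*Protocol*

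**What the plan says.** Protocol section 5.1 sets the Phase 1 contrast: Groups 1 and 2 "will be compared directly on an intention to treat basis according to the randomization of each participant's fire house". It then turns to mixed models and generalized estimating equations for the repeated outcomes and adds: "After adjusting for baseline and time-dependent covariates, changes in the outcomes of interest will be assessed and compared among groups". The covariates are not listed. The adjusted model is not described as secondary, exploratory or a mediation analysis.

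Section 4.6 bears on which covariates could be meant:

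- Under the baseline assessment it says of the questionnaire: "It also includes items on physical activity and other health behaviors to adjust for appropriate covariates".
- Under the follow-up assessments, which take place every 6 months in all consented participants: "The comprehensive nutritional-lifestyle questionnaire will be repeated (detailed above").
- The Phase 1 intervention for Group 1 includes "smaller group (5-20 firefighters) diet and fitness sessions in fire house classrooms and kitchens", and participants who opt in receive "brief text or email messages 2-4 times per week reinforcing the healthy dietary and lifestyle principles". Group 2 receives no intervention in Phase 1.

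**The concern.** An intention-to-treat comparison estimates the whole effect of assigning a fire house to the programme, by whatever route that effect arises. A covariate measured after assignment can itself be a result of assignment. Adjusting for it removes the part of the effect that runs through it. If the covariate and the outcome also share unmeasured causes, the remainder can be biased as well. Mixed models and generalized estimating equations handle correlation between repeated measurements; they do not prevent this.

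The only items that the protocol says it collects for adjustment are physical activity and other health behaviours. They are measured again at each follow-up visit, and the programme contains components that could change them. Section 5.1 as worded therefore allows a model that does not estimate the effect promised in the same paragraph and powered in section 5.2. If the programme raises activity and activity lowers body fat, the expected direction is an effect estimate that is too small.

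**Working it through.** **Inputs.** From the body fat table in section 5.2: SD 6.6, treated 22.7, untreated 24.4, difference 1.7, 250 or 500 per arm. From section 5.1: significance at 0.05, "and all tests will be two-tailed". The share *m* of the effect that runs through adjusted follow-up covariates is not in the documents. It is an assumption, shown from 10% to 50%.

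**The protocol's own figure.** With the normal approximation at the individual level, power = Φ(d / (SD × √(2/n)) − 1.96).

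- 250 per arm: 6.6 × √(2/250) = 0.590; 1.7 / 0.590 = 2.88; Φ(0.92) = 82%, as stated.
- 500 per arm: 6.6 × √(2/500) = 0.417; 1.7 / 0.417 = 4.07; Φ(2.11) = 98%, as stated.

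**With a mediating covariate in the model.** The coefficient for group becomes 1.7 × (1 − m). With the SD held at 6.6:

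| Assumed share m | Difference estimated | Power, 250 per arm | Power, 500 per arm |
|---|---|---|---|
| 0% | 1.70 | 82% | 98% |
| 10% | 1.53 | 74% | 96% |
| 20% | 1.36 | 63% | 90% |
| 30% | 1.19 | 52% | 81% |
| 50% | 0.85 | 30% | 53% |

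Worked line for 30%: 1.7 × 0.7 = 1.19; 1.19 / 0.590 = 2.02; Φ(0.06) = 52%.

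**Check by simulation.** In 1,000 replicates of 500 people with one mediating covariate and no unmeasured common causes, the unadjusted difference stayed at about −1.7. The adjusted difference averaged −1.54, −1.34, −1.20 and −0.84 for shares of 10%, 20%, 30% and 50%. This confirms the algebra. It does not show which share applies here.

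**Limits of the illustration.** A covariate that predicts the outcome also lowers the residual variance, so holding the SD at 6.6 does not give the exact power of the adjusted model; the shrinkage of the estimate remains. The figures carry no allowance for clustering by fire house, because they follow the protocol's own basis. The diet score is far less sensitive: even at 50%, 6.0 becomes 3.0, and 3.0 / (5.6 × √(2/250)) = 5.99, so power stays above 99%.

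**The case against.** The strongest reply is that the harmful covariate is not in the plan. Section 5.1 names none, and a time-dependent covariate could be one that the diet does not affect, such as age or duty status. The sentence about physical activity stands under the baseline assessment and does not say that follow-up values will be used. A covariate list may properly be left to a statistical analysis plan. A reader might infer that the protocol commits to adjusting for follow-up physical activity. The documents do not go that far; this is an inference from several parts of section 4.6.

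Nor do they establish that the programme changes activity. The six planned session topics are all dietary, all 17 items in the table of recommendations are food or drink, and the hypotheses in section 1 concern the diet score, weight and cardiovascular risk. An effect on activity is plausible, given the fitness sessions and lifestyle messages, but it is not shown.

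Finally, section 5.1 labels no model as primary and also lists simple unadjusted tests. A reader might infer that the trial's single main estimate is biased. The text does not support that, since direct comparisons could be reported beside the adjusted models.

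These points limit the finding but do not remove it. It concerns a rule that the protocol states, not a missing list. That rule admits time-dependent covariates into the comparison of groups without restriction. A later analysis plan confined to baseline covariates would depart from it.

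**Conclusion.** The point holds in conditional form. As worded, section 5.1 permits the intention-to-treat comparison to condition on consequences of assignment. If follow-up health behaviours are adjusted for, and if the intervention changes them, the model does not estimate the total effect, and attenuation is the likely direction.

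The size is unknown. For body fat, assumed shares of 10% to 50% give differences of 1.53 to 0.85 instead of 1.7, and power at 250 per arm of 74% to 30% instead of 82%. These figures rest on the assumed share, an SD fixed at 6.6 and no clustering. No single row, such as 52% at a 30% share, should be read as the power of this trial. The correction should be made because the wording undermines a stated aim of the analysis and is easily put right.

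**What to change.** In section 5.1, strike the reference to time-dependent covariates from the sentence on the group comparison, as far as it governs the intention-to-treat models. Adjust those models only for baseline values (baseline outcome, age, sex and data from the existing pre-study medical examination) plus visit time.

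Baseline questionnaire items such as physical activity may be used, with a caveat. Under section 6.1, staff tell each fire house its assignment before members consent, and consent precedes study participation. The baseline questionnaire is therefore completed after assignment is known, and its self-reported answers could be influenced by it. The existing medical examination does not have this weakness.

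Place any model with follow-up behavioural covariates in a separately labelled mediation or exploratory analysis, with its assumptions stated. If only visit time, age or similar variables were meant, say so.

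The cost is a change of wording. No data collection, visit or sample size changes.

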## 5.2. Is there a sample size/power calculation?

☐ No ☒ Yes: If yes; describe the calculation and the scientific rationale, and, if applicable, by site and key characteristics such as participant demographics

Sensitivity analyses have been performed and demonstrate that even in the worst case scenario where only 500 firefighters would be enrolled, the study is well-powered for intention to treat comparisons of Mediterranean Diet Nutritional Intervention (MDNI) vs no intervention. Several conservative examples are given below for very small changes. However, consistent with previous studies, we expect the MDNI to actually produce larger changes that would be more easily measured. The first example assumes the MDNI can achieve a small increase in the mMDS of 6 points (about 1.0 times the population's baseline SD based on our cross-sectional study of mMDS)

For the biomarkers study spearman regression coefficients will be calculated to assess the association between 1) self-reported olive oil consumption, walnuts, tree nuts, other food groups of the Mediterranean Diet and the overall score on the modified Mediterranean Diet scale and the biomarkers. Linear regression models, adjusted for potential confounders will be fitted to study the association of previously mentioned foods and biomarkers. Changes in biomarkers and comparison between groups will be assessed using mixed modeling and generalized estimating equation models or other appropriate statistical tests depending upon the normality

| Population |      |            | Mmds |         |           |            |             |       |
|------------|------|------------|------|---------|-----------|------------|-------------|-------|
| Total      | MDNI | Usual Care | SD   | Treated | Untreated | Difference | Alpha error | Power |
| 500        | 250  | 250        | 5.6  | 27.3    | 21.3      | +6.0       | 0.05        | >99%  |
| 750        | 325  | 325        | 5.6  | 27.3    | 21.3      | +6.0       | 0.05        | >99%  |
| 1000       | 500  | 500        | 5.6  | 27.3    | 21.3      | +6.0       | 0.05        | >99%  |

The second example is for a small body fat change (1.7%) using typical values from our cross-sectional data

| Population |      |            | Body Fat |         |           |            |             |       |
|------------|------|------------|----------|---------|-----------|------------|-------------|-------|
| Total      | MDNI | Usual Care | SD       | Treated | Untreated | Difference | Alpha error | Power |

|      |     |     |     |      |      |      |      |     |
|------|-----|-----|-----|------|------|------|------|-----|
| 500  | 250 | 250 | 6.6 | 22.7 | 24.4 | -1.7 | 0.05 | 82% |
| 750  | 325 | 325 | 6.6 | 22.7 | 24.4 | -1.7 | 0.05 | 94% |
| 1000 | 500 | 500 | 6.6 | 22.7 | 24.4 | -1.7 | 0.05 | 98% |

The third example is for the prevalence of metabolic syndrome. We have found a metabolic syndrome prevalence of about 28% among career firefighters. Based on previous studies, we conservatively expect the MDNI to reverse at least 35% of cases.

| Population |      |            | Metabolic Syndrome Prevalence |         |           |            |             |       |
|------------|------|------------|-------------------------------|---------|-----------|------------|-------------|-------|
| Total      | MDNI | Usual Care | %
Δ                        | Treated | Untreated | Difference | Alpha error | Power |
| 500        | 250  | 250        | -35                           | 18%     | 28%       | -10.0%     | 0.05        | 76%   |
| 750        | 325  | 325        | -35                           | 18%     | 28%       | -10.0%     | 0.05        | 90%   |
| 1000       | 500  | 500        | -35                           | 18%     | 28%       | -10.0%     | 0.05        | 96%   |

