## 1. Specific Aims

1. Develop a multi-pronged, Mediterranean Diet Nutritional Intervention (MDNI) behavior change strategies including: diet/lifestyle education; discounted access to key Mediterranean diet foods; electronic education platforms and reminders. MDNI components will be refined via surveys, literature review and local/national firefighter input including labor/management and fire service focus groups.

Hypothesis (1). Cost-effective, fire-service MDNIs will be developed for the cluster-randomized, career firefighter diet intervention.

2. Cluster Randomized Diet Intervention-Phase I- the Indianapolis Fire Department (IFD) has over 1,000 members. All 44 IFD firehouses will be cluster randomized into two groups and then individual members will be consented regarding study participation. Group 1 will receive an active 12-month MDNI, while Group 2 will receive no intervention. Firefighters categorized as "Administrative Staff" by the IFD will also be approached for participation and if they consent, be assigned to Group 1 because they are not assigned to specific firehouses.

3. Cluster Randomized Diet Intervention -Phase II: Group 1 will cross-over to "self-sustained continuation" for 12 months to examine persistence of behavior change during this less intense, self-directed maintenance diet intervention. Group 2 will cross-over to receive the MDNI for 6 months (assessing a shorter MDNI), followed by a final 6 months of self-sustained continuation. An additional neighboring fire department, Fisher's (IN), will have its 6 firehouses randomized to receive the MDNI (Group 3) or no intervention (Group 4) for six months, and then individual members will be consented regarding study participation. After 6 months, the 3 stations in the MDNI (Group 3) will cross-over to "self-sustained continuation" for the last 6 months to examine persistence of behavior change during this less intense, self-directed maintenance diet intervention. Group 4 will cross-over to receive the MDNI for 6 months (assessing a shorter MDNI).

4. A similar 12-month Cluster Randomized Diet Intervention in the six fire stations of the Fishers (IN) Fire Department with a cross-over by the control group to intervention after 6 months will also be done.

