**4.2. Indicate the study's duration - and the estimated date of study completion**

2 years. December 2018

**4.3. Indicate the total number of participants (if applicable, distinguish between the number of participants who are expected to be screened and enrolled, and the number of enrolled participants needed)**

1,000 career firefighters (500 assigned to group 1 and 500 assigned to group 2). We will approach as many eligible members as possible to consent at least 500 and up to 1,000 participants maximum. For the biomarkers nested study, a total of up to 100 firefighters, selected at random evenly from the existing study arms in Indianapolis

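### The power tables treat firefighters as individually randomised with no loss, so the claim of good power at 500 is unsupported for body fat and contradicted by the table's own figure for metabolic syndrome

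*Protocol*

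**What the plan says.** The unit of randomisation is the firehouse: "All 44 IFD firehouses will be cluster randomized into two groups" (section 1). In section 5.1, Groups 1 and 2 "will be compared directly on an intention to treat basis according to the randomization of each participant's fire house", with alpha 0.05, "and all tests will be two-tailed". Section 4.3 plans "to consent at least 500 and up to 1,000 participants maximum".

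Section 5.2 gives three worked examples at totals of 500, 750 and 1,000:

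- **Diet score (mMDS).** "The first example assumes the MDNI can achieve a small increase in the mMDS of 6 points", with SD 5.6; power is above 99% in every row.
- **Body fat.** A difference of 1.7 points with SD 6.6; power 82%, 94% and 98%.
- **Metabolic syndrome.** 28% untreated against 18% treated, because "we conservatively expect the MDNI to reverse at least 35% of cases"; power 76%, 90% and 96%.

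From these it concludes that "even in the worst case scenario where only 500 firefighters would be enrolled, the study is well-powered for intention to treat comparisons". The tables give sample sizes, SDs or rates, differences, alpha and power. They give no ICC, cluster size, design effect or retention. In all three tables the row for a total of 750 shows 325 per arm; the body-fat row, for example, reads "325 | 325 | 6.6 | 22.7 | 24.4 | -1.7 | 0.05 | 94" per cent.

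**The concern.** Firefighters in one station share a kitchen, meals and shifts, and the intervention works through station champions, group sessions and mailers sent to the firehouse. Outcomes within a station are therefore unlikely to be independent. A power figure that ignores this is too high for the comparison that section 5.1 plans, and so is one that assumes everyone is measured at 12 months.

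Section 5.2 is what justifies 500 as a safe recruitment floor. If its figures are too favourable there, a null result on body fat or metabolic syndrome at that size could be read as absence of effect when the trial had limited ability to detect one. Both outcomes belong to the cardiovascular risk profile named in the hypotheses.

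**Working it through.** **Step 1. Reproduce the printed powers.** Two-sided alpha is 0.05, with individuals independent and no loss. Body fat uses a two-sample t-test with d = 1.7/6.6. Metabolic syndrome uses a two-proportion test of 28% against 18%.

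| n per arm | Body fat | Printed | Metabolic syndrome | Printed |
|---|---|---|---|---|
| 250 | 82.0% | 82% | 75.9% | 76% |
| 325 | 90.6% | 94% (750 row) | 85.9% | 90% (750 row) |
| 375 | 94.1% | – | 90.4% | – |
| 500 | 98.3% | 98% | 96.5% | 96% |

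The 500 and 1,000 rows agree to within one point, so the printed figures contain no allowance for clustering or loss.

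**Step 2. The 750 rows.** 325 + 325 = 650. The printed powers match 375 per arm (375 + 375 = 750). One-sided testing does not explain the row: it gives 94.9% and 91.8% at 325, but 89.2% and 84.6% at 250, against the printed 82% and 76%. The arm counts therefore look like misprints.

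**Step 3. Restate for 44 stations.** The documents give no ICC, so 0.01 to 0.05 is an assumption. Stations are taken as equal in size, 22 per arm.

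- Mean cluster size: m = 500/44 = 11.36, or 1,000/44 = 22.73.
- Design effect: DE = 1 + (m − 1) × ICC.
- Effective n per arm: n_eff = n/DE.
- Power: noncentral t with 44 − 2 = 42 df. The noncentrality is (1.7/6.6)√(n_eff/2) for body fat, and 0.10/√[(0.28×0.72 + 0.18×0.82)/n_eff] for metabolic syndrome.

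Example at N = 500 and ICC 0.05: DE = 1 + 10.36 × 0.05 = 1.518 and n_eff = 250/1.518 = 164.7. The noncentralities are 2.34 and 2.17, giving power of 62.7% and 56.4%.

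| N | ICC | DE | n_eff per arm | Body fat | Metabolic syndrome |
|---|---|---|---|---|---|
| 500 | 0.01 | 1.104 | 226.5 | 76.4% | 70.1% |
| 500 | 0.02 | 1.207 | 207.1 | 72.6% | 66.2% |
| 500 | 0.05 | 1.518 | 164.7 | 62.7% | 56.4% |
| 1,000 | 0.01 | 1.217 | 410.8 | 95.0% | 91.8% |
| 1,000 | 0.02 | 1.435 | 348.5 | 91.3% | 87.0% |
| 1,000 | 0.05 | 2.086 | 239.7 | 78.7% | 72.6% |

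The diet score (d = 6.0/5.6) stays above 99% in every row.

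**Step 4. How much slack body fat has at 500.** By the normal approximation, 80% power needs 236.6 per arm. The largest tolerable design effect is 250/236.6 = 1.057, which is an ICC of about 0.057/10.36 = 0.0055. The largest tolerable loss with zero ICC is 1 − 236.6/250 = 5.4%.

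**Step 5. Credit for baseline adjustment.** Adjusting for a baseline value that correlates r with the outcome multiplies the variance by about 1 − r², so the noncentrality is divided by √(1 − r²). The documents give no r. For body fat at N = 500 with no loss:

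| ICC | r = 0 | r = 0.3 | r = 0.5 | r = 0.6 | r = 0.7 |
|---|---|---|---|---|---|
| 0.01 | 76% | 80% | 87% | 92% | 96% |
| 0.05 | 63% | 67% | 75% | 81% | 89% |

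**Step 6. A harsher scenario.** Take 20% loss and a cluster-size coefficient of variation (CV) of 0.4, so that m = 400/44 = 9.09 and DE = 1 + [(1 + 0.4²) × 9.09 − 1] × ICC. Without adjustment, over the same ICC range, body fat is 67% to 54% and metabolic syndrome 61% to 49%. Neither the loss nor the CV comes from the documents.

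**The case against.** The strongest reply is that section 5.1 plans mixed or GEE models adjusted for baseline, whereas the body-fat SD of 6.6 is cross-sectional. Step 5 shows that a correlation of about 0.3 at ICC 0.01, or about 0.6 at ICC 0.05, brings body fat back to about 80% at 500 with no loss. This stands. A reader might infer from Step 3 that the trial is underpowered for body fat at 500. The documents do not support that, because the answer turns on an ICC, a retention and a correlation that none of them states. The reply does not rescue the printed claim either: section 5.2 states no correlation and takes no such credit, and section 5.1 also lists unadjusted t-tests.

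Other replies have partial force:

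- The rows are labelled as examples, 500 is called a worst case, and larger effects are expected. That does not make the stated powers right for the stated effects and design.
- Section 7.1 reports that about 90% of those approached in an earlier study in this department consented and completed it. This does not establish 12-month retention here, but it is a reason to treat 20% loss as a scenario only.
- The 750 rows might be taken as evidence of wrong power calculations. They are not: the powers are right for a total of 750, only the arm counts are wrong, and nothing at 500 depends on them.
- Detail may be left to a statistical analysis plan. The point here is what the protocol prints, not what it leaves out.

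**Conclusion.** The point holds in a limited form. Without any assumption: the printed powers are for individually randomised people with complete follow-up, not for 44 randomised firehouses; the claim at 500 is contradicted for metabolic syndrome by the protocol's own 76%, judged against the conventional 80%; and the arm counts in the 750 rows are misprinted in all three tables.

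The size of the overstatement rests on the assumed ICC of 0.01 to 0.05 and the other conditions of Step 3 (equal clusters, no loss, no adjustment). Under these, body fat at 500 is 6 to 19 points below its stated power and metabolic syndrome 6 to 20 points below. At 1,000 the gaps are 3 to 19 and 4 to 23 points. For body fat the conclusion is that adequate power at 500 has not been shown, not that it is absent. The diet-score claim is sound throughout.

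**What to change.** Rewrite section 5.2:

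1. Restate the three tables for 44 stations, with a design effect over a stated ICC range, cluster-based degrees of freedom and an assumed retention.
2. If credit is taken for baseline adjustment, state the baseline-outcome correlation used.
3. Correct the arm counts in the 750 rows of all three tables to 375/375.
4. Limit the statement about 500 to the diet score. Say that metabolic syndrome is below 80% at that size, and that body fat depends on the ICC, retention and baseline correlation.

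The cost is one rewritten section. It needs no extra participants or procedures, but the stated figures become less favourable.
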